### 2.4. Methods: Monitoring

#### 2.4.1. Harms

To our knowledge, the Pavlik harness has a low-risk profile, although there have been described some rare cases of femoral nerve palsy and avascular necrosis of the femoral head [40].

Regarding security variables, during the follow up, the following will be recorded: confirmation of the good enough position of the Pavlik harness in the revisions carried out every four weeks; note down any treatment difficulties for the patient (such as chafing, maladaptation, crying, etcetera) and identify any concomitant pathologies that have arisen during the period of treatment with the harness to assess whether this involves discomfort or difficulty for the patient and family; interview parents about their ability to adapt in daily activities such as breastfeeding, playing, changing nappies and clothes.

Likewise, a review will be conducted in a face-to-face consultation at 6–9 months in the treatment group to check the correct state of the locomotor apparatus.

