#### 2.1.5. Modifications

The patient will be monitored for concomitant pathologies that have arisen during treatment with the Pavlik harness to assess whether they will cause discomfort or difficulty for the patient and their family. In case of incompatibility, treatment with the Pavlik harness will be withdrawn.

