#### 2.1.6. Adherence

A face-to-face evaluation of the subjects in the treatment group will be conducted after four weeks to assess the correct use of the harness.

It is beneficial to check daily the flexion creases of the knees, groin, and neck to identify possible chafing of the skin, in which case soft padding is applied to cover the straps.

During the first visit, the patient’s parents will learn recommendations for daily situations such as nappy changing, dressing, resting, breastfeeding, playing, and bathing at home. They will also receive a complete written guide. On the second visit, the researchers will interview the parents to learn about daily life adaptations such as breastfeeding, play, nappy changing, and dressing.

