#### 2.1.9. Participant Timeline

During the first four to six weeks of life, a bilateral knee ultrasound will be performed on neonates with a breech presentation to determine the sulcus angle. Then, they will be derived into the Pediatric Orthopedics and Traumatology Department, as stated in Figure 2.

Intervention group: The estimated duration of the Pavlik harness procedure is two months, with four-week revisions by a pediatric orthopedic surgeon. After two months, a pediatric radiologist will perform a second ultrasound to evaluate the sulcus angle, and the Pavlik harness will be removed. In both groups, a face-to-face consultation in pediatric orthopedic surgery will be performed at 6–9 months to assess the clinical progression, as shown in Figure 3.

Control group: the control group will be evaluated two months after the baseline ultrasound, with a second one performed by a pediatric radiologist, as shown in Figure 4.

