### 2.3. Methods: Data Collection, Management, and Analysis

#### 2.3.1. Data Collection Methods

Ultrasound examination will be performed with the patient in a supine position and the knee placed at 45–90° of flexion. The positioning of the transducer must be in a transversal plane perpendicular to the axis of the femoral diaphysis. This way, the femoral condyles, the trochlea, and the ossification centre are visible.

Likewise, the following variables will be documented:Age;Sex;Birth weight;Birth presentation (footling, frank or complete breech);Presentation at the last ultrasound performed during pregnancy;Coxofemoral joint status according to clinical (Graf classification [39]: I = normal, II = unstable, III and IV = off-centre) and sonographic parameters (α angle).

Based on the review by the pediatric orthopedic surgeon, the following variables will be controlled:Verification of the suitable position of the harness during the check-ups performed every four weeks until two months;Treatment difficulties and adverse reactions: blistering, inadaptation, crying, femoral nerve palsy, avascular necrosis of the femoral head;The discrepancy of inferior limb length;Skin folds asymmetry;Knee articular balancing: complete and symmetrical, uncomplete of one knee, uncomplete of both knees;Articular click;Patellar displacement: tolerated, apprehension in the form of crying or discomfort.

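### In the two treatment months, harms that are not specific to the device are scheduled for recording around the harness, so common infant events would lack a concurrent randomised comparator

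*Protocol article*

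**What the plan says.** All references are to the protocol article.

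- **2.4.1 Harms.** Besides harness position at the four-weekly revisions, staff are to "note down any treatment difficulties for the patient (such as chafing, maladaptation, crying, etcetera", to "identify any concomitant pathologies that have arisen during the period of treatment with the harness", and to "interview parents about their ability to adapt in daily activities such as breastfeeding, playing, changing nappies and clothes".
- **2.1.5 Modifications.** Monitoring has the same window: "The patient will be monitored for concomitant pathologies that have arisen during treatment with the Pavlik harness".
- **2.1.6 Adherence.** The interim visit is for one arm: "A face-to-face evaluation of the subjects in the treatment group will be conducted after four weeks". The parent interview at the second visit is described in this same section.
- **2.1.9 Participant Timeline.** Under the intervention group: "The estimated duration of the Pavlik harness procedure is two months, with four-week revisions by a pediatric orthopedic surgeon". For controls: "the control group will be evaluated two months after the baseline ultrasound, with a second one performed by a pediatric radiologist". An orthopaedic consultation at 6–9 months is stated for both groups.
- **2.4.1 Harms, last paragraph.** The 6–9 month review is stated for the treatment group.
- **2.3.1 Data Collection Methods.** The list drawn from the orthopaedic surgeon's review includes "Treatment difficulties and adverse reactions: blistering, inadaptation, crying, femoral nerve palsy, avascular necrosis of the femoral head", along with limb length, skin folds, knee motion, clicks and patellar displacement. No arm is named. Only the harness-position item carries a time.

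**The concern.** The recorded items are of two kinds. Strap chafing, harness position and adapting nappy changes to the harness exist only where there is a harness and need no control. Crying, a new concomitant illness and trouble with feeding or daily care also arise in infants who wear nothing. For that second kind, the randomised control arm is what shows how much is ordinary infancy and how much comes with the harness.

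If these items are collected only at harness visits, the trial randomises but gives up that comparison. A report that several treated infants cried or fed poorly could then be read as a harness effect or dismissed as normal, and the data would support neither reading. This matters because the article presents the trial as the first use of the harness for this condition. Its Discussion also says that families may be hard to persuade and to keep compliant.

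**Working it through.** No figure in the plan is in dispute on this point, so the main check sets the text side by side by arm.

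| Time | Harness arm | Control arm |
|---|---|---|
| Baseline | Ultrasound, orthopaedic examination, caregiver guidance (2.1.4, 2.1.6) | Ultrasound, referral to orthopaedics (2.1.9) |
| Four weeks | Face-to-face evaluation (2.1.6); orthopaedic revision (2.1.9) | No contact stated |
| Two months | Orthopaedic revision, ultrasound, harness removed (2.1.9) | Ultrasound by the radiologist (2.1.9) |
| 6–9 months | Orthopaedic consultation (2.1.9, 2.4.1) | Stated for both groups in 2.1.9; 2.4.1 mentions only the treatment group |

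**Step 1: recording windows.** Sections 2.1.5 and 2.4.1 define the window for concomitant pathologies by harness treatment, a period that controls do not have. The crying item in 2.4.1 is worded as a difficulty of treatment.

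**Step 2: opportunity.** The list in 2.3.1 comes from the orthopaedic review. Within the two months, that review is scheduled in the text only for the harness arm. The controls' two-month attendance is an ultrasound, and the article asks nothing of caregivers there.

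**Step 3: can the 6–9 month visit fill the gap?** The first scan is at four to six weeks of life. Assume that the eight weeks of treatment start straight after it and that 6–9 months means age. The window then closes at 12 to 14 weeks of age (4 + 8 and 6 + 8). Six months is about 26 weeks, so the visit comes at least 26 − 14 = 12 weeks later. If 6–9 months is counted from the start of treatment, the gap is at least 26 − 8 = 18 weeks. Either way it is late for recalling crying or feeding, and its stated purpose is clinical progression (2.1.9) or the locomotor system (2.4.1).

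**Step 4: what could parallel recording show?** The sample size in 2.1.10 reproduces: n = 2(1.960 + 0.842)² × 5.78² / 10² = 5.24 (stated 5.25, a rounding difference), hence 6 per group. With 6 per arm:

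- No events in 6 infants gives a one-sided 95% upper limit of 1 − 0.05^(1/6) = 0.39.
- Fisher's exact test at 0.05 (two-sided) rejects only for 5 v 0, 6 v 0 or 6 v 1 events, or the reverse.
- For assumed true rates of 80% v 20%, power is 0.393 × 0.262 + 0.262 × 0.262 + 0.262 × 0.393 = 0.27.
- For assumed rates of 50% v 10%, it is 0.094 × 0.531 + 0.016 × 0.531 + 0.016 × 0.354 = 0.06.

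The article gives no event rates; these are assumptions that span a large and a moderate-to-large difference. Parallel recording would therefore give a descriptive comparison, not a test.

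**The case against.** **The one-arm reading is inferred.** No sentence says that control events go unrecorded. The two timeline figures cannot be seen, and the study-setting section has both departments following patients without naming an arm. The blinding section has patients attending check-ups without the harness, which would be compatible with control check-ups. A condensed article may also leave case-report forms to the full protocol. This stands as a limit on certainty. Even so, the article does state visits and recording windows by arm, and it says both groups where it means both.

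**The list in 2.3.1 could apply to both arms.** It could. Apart from harness position, its items have no timing, and the knee, click, skin-fold and patellar items would suit the 6–9 month visit. A reader might infer that they are collected during treatment in one arm only, but the text does not establish that.

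**The purpose is tolerability monitoring.** No safety outcome or between-arm harm test is planned. A reader might infer that the trial will report a spurious excess of harm in the harness arm; the documents do not support that. What stands is narrower: tolerability findings for common events will have no concurrent reference.

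**Recording in controls would not settle attribution.** This is correct at six per arm with unblinded caregivers, since parental reports may differ with knowledge of the allocation.

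**Serious harms.** A reader might also infer that 2.4.1 leaves femoral nerve palsy and avascular necrosis unrecorded. It does not follow: 2.4.1 names both as known risks, its own list is open-ended, and 2.3.1 records both.

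**Conclusion.** The point holds as a cheap improvement to data collection. On the text shown, items that are not device-specific are tied during the two treatment months to harness treatment and its revisions. Controls have no stated contact at which to report them before 6–9 months, other than a scan. Whether they attend at 6–9 months is itself stated inconsistently.

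The size is modest. The primary sulcus-angle comparison is untouched, harness-specific events need no control, and at the minimum sample size the gain is a side-by-side description. The conclusion assumes that the unseen figures and any fuller protocol add no control contact; if they do, the remedy reduces to stating it. The documents do not support going further and saying that control harms are definitely unrecorded, or that better recording would allow firm attribution.

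**What to change.** - In 2.3.1 and 2.4.1, separate device items from non-device items. Collect the non-device items (crying, new concomitant pathology, feeding and other daily-care difficulty) with one short caregiver questionnaire, worded identically in both arms.
- Give it at the two-month attendance that both arms already make, by someone other than the blinded radiologist and away from the scan. If feasible, add four weeks, by telephone for controls.
- State in 2.3.1 which arm and which visit each orthopaedic item belongs to.
- Keep harness-fit, strap and harness-withdrawal items (2.1.5) in the harness arm.
- Report the shared items descriptively by arm, noting the small numbers and the unblinded caregivers.
- Reconcile 2.1.9 and 2.4.1 on who attends at 6–9 months.

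The cost is one shared page in the data notebook and, if the four-week contact is added, one call per control family (about six at the stated minimum). The downside is a slight added burden on control families. No treatment or endpoint changes.

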#### 2.4.2. Auditing

Frequency and procedures for auditing trial conduct, if any, and whether the process will be independent of investigators and the sponsor will be conducted by the hospital Research Ethics Committee.

## 3. Discussion

TD is a condition identified late and usually requires an invasive treatment when symptomatic.

The possibility of TD being a developmental entity could attain its early diagnosis before patients become symptomatic during adolescence or early adulthood when it is too late for the skeleton to remodel, usually requiring aggressive surgical interventions.

Developmental dysplasia of the hip is a condition that presented a prognosis similar to TD before the introduction of the Pavlik harness. Both conditions have been associated [23,27], so it is plausible to assume they share some common risk factors. In our study, we hypothesize that the breech presentation is a risk factor for TD, as shown in previous human [28] and animal [26] studies. In DDH, a subluxated or dislocated femoral head precipitates the development of a shallow and abnormal acetabulum. Likewise, an extended leg during the breech fetal position could play a similar pathological process as a lack of mechanical forces on the femoral trochlea could precipitate the development of a shallow trochlear sulcus. Thus, we decided to select the newborns in breech presentation as a target group to obtain sonographic data to define radiological values for the dysplastic trochlea. This would serve as a guide for a future screening method that would help identify TD early.

Given that TD may be a developmental process, early diagnosis in the neonatal period could allow for an intervention such as DDH. The Pavlik harness is a treatment option that would maintain the knees bent using the patella to help mold the trochlea in a similar way it is used to make the femoral head mold the acetabulum. Although safe, this treatment is not exempt from certain difficulties in the daily tasks of caring for the newborn, such as nappy changing or dressing. This manifests as a struggle to convince the caregivers of the patient of the future benefits of the Pavlik harness and for compliance, as TD is a condition that usually manifests later in life; thus, the results are not tangible in the short term.

We will conduct a randomized controlled trial to validate the hypothesis that trochlear dysplasia can be treated non-invasively early in life with a Pavlik harness.

Ours is a single-centre study, so the results may not be directly generalized to other centres and the general population. Furthermore, since this is a short-term study, we need to find out the long-term effects of correcting TD with the Pavlik harness or its efficacy compared to other already established treatments for TD, such as MPFL reconstruction or trochleoplasty. We also only assess two months of treatment duration, so there could be more appropriate cost-effective modalities with the Pavlik harness. TD and DDH often present concomitantly, but DDH constitutes an exclusion criterion in our study, so further research will be necessary for these patients to address the best position and regimen of the Pavlik harness for treating both conditions. However, from this study, we can learn about the breech presentation as a risk factor for TD and provide information for future studies on long-term intervention, as ours is the first trial using the Pavlik harness for treating TD.

## Figures and Tables

**Figure 1 jpm-13-00796-f001:**
[figure not shown]
Study design. The newborns in the breech position will be screened with an ultrasound test for dysplastic sulcus angles (≥159°). Then, they will be divided into a 1:1 randomization, either into the intervention group or the control group. A blinded observer will perform a second ultrasound, from which the data for the outcomes will be collected.

**Figure 2 jpm-13-00796-f002:**
[figure not shown]
ORLIMAN (Valencia, Spain) Pavlik Harness with the knees placed at a flexion of 90° [35].

**Figure 3 jpm-13-00796-f003:**
[figure not shown]
Intervention group timeline.

**Figure 4 jpm-13-00796-f004:**
[figure not shown]
Control group timeline.

## Data Availability

Source documents are all original documents, data, and records. All data collected for this study, both for the preparation of the subject’s clinical history and for the rest of the study documents, will be filed in the participating centres, on paper or in digital format, by the procedures of each centre. A numerical code will identify the data collected for the study, and only the principal investigator/collaborators will be able to relate these data to the patient and their medical history. Access to information on participating subjects will be restricted to the study doctor and authorized collaborating team members. The investigator and the centre will guarantee direct access to the source data or documents to the personnel authorized by the sponsor (monitor, auditor), the health authorities (Spanish Agency of Medicines and Health Products), and the Clinical Research Ethics Committee, when required. Patient data will be collected in a data collection notebook (CRD). The principal investigator or a sub-investigator at the site must ensure the accuracy and completeness of the data recorded and sign the appropriate CRDs. When the database has been deemed complete and accurate, it shall be closed by locking the database. All relevant documents related to the study will be archived according to the requirements of the ICH-GCP, the Commission Directive 2005/28/EC of 8 April 2005, and according to the relevant national laws. The data will be included in a database that must comply with Regulation 679/2016, of 27 April General Data Protection Regulation and Organic Law 3/2018, of 5 December, on personal data protection and guarantee of digital rights. Likewise, the transmission of said data will be carried out with the appropriate security measures in compliance with said regulation. Patients will only be identified by their patient code during documentation and analysis, while the researcher will keep all subject names secret. The investigators are obliged to keep all study data and information confidential and to use these data only in the context of the persons involved in the conduct of the study. Study material or information generated in this study should not be made available to third parties except by official sponsor representatives or regulatory authorities.
